## Abstract

**Background:**

After experiencing a stroke, most individuals also suffer from cardiac disease, are immobile and thus have low endurance for exercise. Aerobic capacity is seriously reduced in these individuals and does not reach reasonable levels after conventional rehabilitation programmes. Cardiovascular exercise is beneficial for improvement of aerobic capacity in mild to moderate stroke. However, less is known about its impact on aerobic capacity, motor recovery, and quality-of-life in severely impaired individuals. The aim of this pilot study is to explore the clinical efficacy and feasibility of cardiovascular exercise with regard to aerobic capacity, motor recovery, and quality-of-life using feedback-controlled robotics-assisted treadmill exercise in non-ambulatory individuals soon after experiencing a stroke.

**Methods/Design:**

This will be a single-centred single blind, randomised control trial with a pre-post intervention design. Subjects will be recruited early after their first stroke (≤20 weeks) at a neurological rehabilitation clinic and will be randomly allocated to an inpatient cardiovascular exercise programme that uses feedback-controlled robotics-assisted treadmill exercise (experimental) or to conventional robotics-assisted treadmill exercise (control). Intervention duration depends on the duration of each subject’s inpatient rehabilitation period. Aerobic capacity, as the primary outcome measure, will be assessed using feedback-controlled robotics-assisted treadmill-based cardiopulmonary exercise testing. Secondary outcome measures will include gait speed, walking endurance, standing function, and quality-of-life. Outcome assessment will be conducted at baseline, after each 4-week intervention period, and before clinical discharge. Ethical approval has been obtained.

**Discussion:**

Whether cardiovascular exercise in non-ambulatory individuals early after stroke has an impact on aerobic capacity, motor recovery, and quality-of-life is not yet known. Feedback-controlled robotics-assisted treadmill exercise is a relatively recent intervention method and might be used to train and evaluate aerobic capacity in this population. The present pilot trial is expected to provide new insights into the implementation of early cardiovascular exercise for individuals with severe motor impairment. The findings of this study may guide future research to explore the effects of early cardiovascular activation after severe neurological events.

**Trial registration:**

This trial is registered with the Clinical Trials.gov Registry (NCT01679600).

## Background

Cardiovascular-related diseases are the leading causes of death [1] and long-term disability worldwide [2]. Stroke affects about 15 million people each year, whereby 5 million die and another 5 million remain permanently disabled [3]. It has been estimated that stroke will occur in 35% of the population over the age of 65, a group that will increase in proportion due to demographic shifts in most populations [4]. This leads to an increased need for effective rehabilitation programmes to enhance recovery, improve functional status and quality-of-life, while considering the future challenges in worldwide health care economics [5].

To date, stroke rehabilitation research has focussed primarily on restoring motor control to promote independent function during daily life. However, around 75% of post-stroke individuals suffer from cardiac disease [6,7], and the majority have low endurance for exercise as a consequence of immobility [8]. Previous work has shown that peak oxygen uptake (VO_2_peak) is reduced to 10 to 17 mL/min/kg within the first 30 days after stroke [9-11] and does not rise over 20 mL/min/kg after 6 months [11-14]. These values are 25 to 45% lower than VO_2_peak in age-matched healthy subjects [15,16]. This early and persistent decline in aerobic capacity can delay or inhibit participation in a therapeutic exercise programme, cause difficulties in the rehabilitation process and long-term post-stroke course of care, and limits an individual’s independent performance of functional activities [7,17].

In a recent meta-analysis it has been shown that cardiovascular exercise is beneficial for improving VO_2_peak and walking endurance in mild to moderately impaired individuals in sub-acute stroke (1 week to 6 months after onset) [18]. However, less is known about its impact on motor recovery, quality-of-life, and mortality. Previous trials did not consider post-stroke individuals with severe motor impairments due to the challenge of selecting appropriate training modalities and evaluation of effectiveness (for example, aerobic capacity). About 50% of stroke survivors may be non-ambulatory or even unable to walk a speed or distance necessary to achieve aerobic benefits [19]. This leads to inadequate training programmes and restricts the performance of valid cardiopulmonary exercise testing protocols. Given the fact that most motor recovery occurs in the first 3 months after a stroke [20], sub-acute rehabilitation programmes have to target neuromuscular recovery as well as cardiovascular exercise to optimize intervention outcomes. This could be achieved by the implementation of assistive devices to promote functional activities such as walking or stair climbing.

The application of robotics-assisted walking thus has substantial clinical potential. The technology offers several advantages over conventional rehabilitation strategies, such as motor function related training programmes within controlled evaluation settings, even for individuals with severe motor impairments. Robotics-assisted treadmill exercise (RATE), consisting of driven gait orthoses with an integrated body weight unloading system, opens new perspectives for cardiovascular exercise and evaluation of aerobic capacity in the early stages after stroke.

A novel assessment protocol has been developed to estimate key cardiopulmonary performance parameters during RATE [21,22]. This incorporates a human-in-the-loop feedback mechanism, which allows individuals to maximise their voluntary input and associated cardiovascular stress. A previous study provided evidence for the concept of feedback-controlled RATE (FC-RATE) to evaluate aerobic capacity and guide cardiovascular exercise in non-ambulatory individuals with sub-acute stroke [23]. Cardiopulmonary performance parameters yielded reasonable values following standardised exercise testing protocols. The next logical step is to evaluate the clinical efficacy and feasibility of the concept during early stroke rehabilitation. It has been hypothesised that FC-RATE is feasible and effective for maintenance or improvement of aerobic capacity in non-ambulatory individuals with sub-acute stroke. This might be highly relevant for further research to explore the association between cardiovascular rehabilitation and neural plasticity during early stroke rehabilitation.

This randomised controlled pilot trial aims: (1) to explore the clinical efficacy of early cardiovascular exercise on aerobic capacity, motor recovery, and quality-of-life; (2) to evaluate the feasibility of FC-RATE for cardiovascular rehabilitation in non-ambulatory individuals after stroke; and (3) to put forward recommendations for development and design of larger clinical trials regarding cardiovascular rehabilitation early after stroke.

## Methods/Design

All procedures involved in this trial will be conducted in compliance with national ethical standards and the Helsinki Declaration. Ethical approval has been obtained from the ethics committee of the canton of Aargau in Switzerland (Reference No. 2012/051).

### Design and setting

This study is a single-centred single blind, randomised control trial with a pre-post intervention design. Subjects will be recruited at a neurological rehabilitation clinic in the northwestern part of Switzerland (Reha Rheinfelden). Figure 1 illustrates the plan of the study protocol.

**Figure 1 F1:**
[figure not shown]
**Flow chart outlining the study protocol.** A 4-week intervention period includes baseline assessments (t0) and first post-intervention (t1) assessments (solid line). The dashed line represents a potential continuation of the intervention due to extended inpatient rehabilitation. Post-intervention assessments will be conducted after every 4-week intervention period and before clinical discharge.

### Eligibility criteria

Subjects will be enrolled after their first stroke if they are non-ambulatory. Inclusion criteria are: (1) clinical diagnosis of an initial stroke, (2) ≤20 weeks post-stroke at intervention onset, (3) age ≥18 years, (4) Functional Ambulation Category (FAC) ≤3, and (5) ability to understand the procedures and provide informed consent. Exclusion criteria are: (1) contraindications for cardiopulmonary exercise testing as outlined by the American College of Sports Medicine (ACSM) [24], (2) contraindications for RATE according to the device manufacturer, (3) concurrent neurological disease, (4) concurrent pulmonary disease, and (4) history of dementia.

### Recruitment

Potential subjects will be screened daily by searching the admission lists of the rehabilitation centre. The project leader will approach eligible subjects and explain the purpose of the study and ask whether potentially qualifying individuals have an interest in participating. If a potential subject expresses interest, the study will be explained in detail, all questions will be addressed and the subject will be invited to participate by providing signed informed consent. Subjects then will be referred for specific cardiac examination by a cardiologist to detect potential contraindications for cardiopulmonary exercise testing. The project leader and the responsible physician will make a final decision on inclusion.

### Randomisation, allocation concealment, and blinding

Subjects will be randomly allocated to an experimental group (FC-RATE) or to a control group (RATE). An independent researcher will generate a 4-block randomisation list and send it to the clinic's pharmacy for safekeeping. The leader of the physical therapy team will call the pharmacy to request a subject’s allocation. Only the treating therapists will have access to the allocated documents. The project leader, who is blind for allocation of the subjects, will carry out all testing procedures as an independent examiner. A further research assistant will be responsible for data input. Subjects will be told not to talk to the examiner about the group allocation or therapy content during the post-intervention assessments. Randomisation will be concealed to the independent examiner until the last post-intervention assessment has been performed. The data will be analysed by the project leader.

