### Data management and analysis

Data will be recorded on standardised forms and concealed between examiners and therapists. All data recorded continuously during testing will be saved automatically by the software module and will only be accessible by an independent software specialist. Data set examples will be checked for errors randomly or at any time a serious adverse event occurs. Raw breath-by-breath data will be processed using a zero phase shift moving average filter over 15 breaths [39]. Peak cardiopulmonary response variables will be calculated by analysing the final 30 s during incremental exercise, whereby criteria for maximal aerobic capacity will be (1) plateau in oxygen uptake, (2) respiratory exchange ratio (RER) ≥1.15, and (3) peak heart rate within 10 beats per minute of the age-predicted heart rate maximum (adjusted for subjects on β-blocker medications) [24]. Further peak performance variables will be defined as the maximal values at the termination time of the IET. The gas exchange threshold (GET) will be estimated using the v-slope method and standard gas exchange criteria [40]. Step response kinetics will be calculated using a non-linear least-squares algorithm to fit the data as described in the following mono-exponential equation: VO_2(t)_=VO_2_(b)+ΔVO_2_(1-e^-(t-Td)/τ^), t > 0, with VO_2_(b) = oxygen uptake at baseline, ΔVO_2_ = step increase in oxygen uptake, Td = time delay of 20 s corresponding to the cardiodynamic phase of the response, and τ = time constant [34]. Steady-state will be defined as the mean value of the final 120 s during constant load phases. All analyses will be performed using MATLAB (Version R2010a, MathWorks, Natick MA, USA) and MetaSoft (Version 3.9.6 SR1, Cortex Biophysik GmbH, Leipzig, Germany).

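### The project leader is both blinded examiner and analyst, and concealment is tied to the last assessment instead of to a lock of readings and test choices

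*Protocol article*

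**What the plan says.** Four roles described in the protocol article fall to the project leader.

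- Recruitment: "The project leader will approach eligible subjects and explain the purpose of the study".
- Inclusion, shared with a physician: "The project leader and the responsible physician will make a final decision on inclusion".
- Testing, while blinded: "The project leader, who is blind for allocation of the subjects, will carry out all testing procedures as an independent examiner".
- Analysis: "The data will be analysed by the project leader".

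The end of concealment is stated just before the analyst is named: "Randomisation will be concealed to the independent examiner until the last post-intervention assessment has been performed". The allocation list comes from someone else and is kept by the pharmacy: "An independent researcher will generate a 4-block randomisation list".

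Two further arrangements separate data handling from the examiner: "A further research assistant will be responsible for data input"; and, under Data management and analysis, the continuous test recordings "will be saved automatically by the software module and will only be accessible by an independent software specialist". The same section keeps the recording forms concealed between examiners and therapists.

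**The concern.** The trial takes care to blind the person who conducts the tests. That protection is tied to an assessment and not to the point where readings are final, data are locked or the analysis is fixed. Because the examiner is also the analyst, the blinding can lapse just when the recordings are turned into outcome values and the tests are chosen. The article mentions neither coded arms nor a separate blinded reader.

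At stake is unconscious preference in the steps that need judgement. The Conclusion section makes these results the basis for deciding whether full-scale trials are warranted.

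A second issue lies in the word used for the end point. Each subject has a series of follow-up assessments, so the last one could mean that subject's last or the trial's last. If it means the subject's, the person who approaches patients and shares the inclusion decision would learn past allocations while enrolment continues under small blocks.

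**Working it through.** The plan states no figure to reproduce here. The check sets the sections side by side and then sizes what can be sized.

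**1. Order of events.** Concealment ends at an assessment. GET estimation, the criteria for a maximal test and the statistical tests (Data management and analysis; Statistical analysis) have no stated timing relative to that point. No reader or analyst other than the project leader is named.

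**2. Which steps leave room for judgement.**
- GET: listed among the primary outcomes in Table 1. It is read by v-slope and gas exchange criteria, with no blinded or second reader.
- Oxygen-uptake plateau: a criterion for maximal aerobic capacity, with no numerical definition.
- Normality: decides between t-test and Mann-Whitney U, with no stated rule.
- Emphasis: Table 1 lists 16 primary parameters and ranks none. At 0.05 each, and assuming independence, the chance of at least one false positive at one time point is 1 − 0.95^16 = 0.56. The correlation between these parameters is not given, so this is only an indication of scale.

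Steps that follow fixed rules: VO2peak (final 30 s), steady state (final 120 s), the 15-breath filter, the kinetic fit (given equation, 20 s delay, least squares) and covariate entry (significant at baseline).

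**3. Size of the test choice.** In 20,000 simulated normal data sets with no effect, either test was allowed to count if significant.
- 7 per arm: 4.8% for the t-test alone, 5.2% for either test.
- 10 per arm: 5.1% for the t-test alone, 5.9% for either test.

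The increase is below one percentage point per endpoint.

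**4. Per-subject release.** Assumptions: blocks of size four, two per arm, with block size and boundaries known to the project leader. The six possible orders are equally likely.
- All earlier block members finished: position 4 is always certain. Position 3 is certain if the first two match, with probability 2/6 = 1/3. Share certain = (0 + 0 + 1/3 + 1)/4 = 33%, or 6.7 of 20 subjects. Correct guesses = (1/2 + 2/3 + 2/3 + 1)/4 = 71%.
- The most recent subject still in the trial: only position 4 can be certain, with probability 1/3. Share certain = (1/3)/4 = 8%, or 1.7 of 20. Correct guesses = (1/2 + 1/2 + 2/3 + 2/3)/4 = 58%.
- The two most recent still in: none certain. Correct guesses = (1/2 + 1/2 + 1/2 + 2/3)/4 = 54%.

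Which case applies depends on spacing. Trial status gives a start in 2012 and the end of enrolment in June 2014, so about 18 to 30 months (78 to 130 weeks). Twenty evenly spaced subjects would then arrive 78/20 = 3.9 to 130/20 = 6.5 weeks apart. At 24 months the gap is 104/20 = 5.2 weeks. The Intervention section gives typical stays of 4 to 12 weeks. With a 5.2-week gap, a 4-week stay gives 33% certain, an 8-week stay 8% and a 12-week stay 0%.

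**The case against.** The strongest case on the other side has five parts.

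- **Timing is inferred.** The article does not say that the analysis waits for the allocation. A reader might infer that the data are certain to be analysed unblinded; the text only leaves this possible. This stands, and limits the point to what nothing prevents.
- **Most readings are rule-based.** A reader might infer that the kinetic fits, the covariates or VO2peak are open to the analyst's preference. The documents do not support that: the fit and the covariate rule are fixed, and VO2peak is a 30 s window that does not depend on the plateau. This stands, and narrows the exposure to the four items listed in the working.
- **Inclusion is a joint decision, and per-subject release is the less natural reading.** The article speaks of randomisation as a whole, restricts the allocation documents to the treating therapists and describes the leader as blind. A reader might infer that a third of allocations are predictable. That needs per-subject release and every earlier block member to have finished, so it is only the top of the range. This stands; the block arithmetic supports a clarification of wording and no more.
- **There are safeguards.** Separate data input, restricted access to recordings and concealed forms all help. None keeps the analyst blind once the allocation is released.
- **It is a pilot that claims only single blinding, and lock procedures often sit in a fuller document.** An unblinded analyst does not contradict the single-blind label. But the article itself fixes both the release point and the analyst, so the point concerns what it states and not omitted detail.

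**Conclusion.** The point holds in a limited form. The article ends the project leader's concealment at an assessment and makes the same person the analyst. It therefore does not secure blinding for the GET reading, the plateau judgement, the parametric or non-parametric choice, or the emphasis among 16 primary parameters. This assumes that the project leader makes those readings, which the article implies by naming no one else.

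The bias in GET or in emphasis cannot be quantified from the document. The choice of test matters little on its own. Predictability of allocation arises only if release is per subject; it then lies between 0 and 33% of allocations, according to overlap. If release is trial-wide, this route is closed. Nothing here shows that any reading or inclusion decision would in fact be biased. It is a cheap improvement, not a fatal flaw.

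**What to change.** State that allocation stays concealed from the project leader until two conditions are met: the last assessment of the last subject in the whole trial has been done, and the GET readings, plateau judgements and test choices are final and locked.

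Run the analysis on arms coded A and B. The key should stay with the independent researcher who generated the list or with the pharmacy that keeps it.

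Withhold the training heart rate and perceived-exertion data from the analyst until that lock. The two arms have different targets for both (40 to 70% against at most 30% of heart rate reserve; 11 to 14 against at most 7 on the exertion scale), so these data would reveal the code.

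Coding hides the direction of a difference but not its significance, so it limits selective emphasis without removing it.

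The cost is a small amount of extra data handling and a short delay before release. No extra staff are needed.

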### Outcome measures

All primary and secondary outcome measurements will be carried out at baseline (t0), after each 4-week intervention period (t1, t2, t3, *etcetera*), and before clinical discharge. At baseline, descriptive variables for each subject include age, sex, area and type of infarct, side of stroke, time since stroke onset, body height and body mass.

A summary of the primary and secondary outcome measures can be found in Table 1. The primary outcome will be aerobic capacity, the accepted criterion for exercise capacity [24]. We will estimate standardised cardiopulmonary performance parameters based on international guidelines [25]. Secondary outcome measures will focus on physical performance, stroke impact, and feasibility. We will evaluate the work rate tracking error during FC-RATE by calculating the root mean square error (RMSE) between actual work rate and target work rate values. Gait speed will be assessed using the 10 Meter Walk Test (10MWT) [26,27]. Walking endurance will be measured using the 6 Minute Walk Test (6MWT), the distance that an individual is able to walk in 6 minutes on a hard, flat surface [28,29]. To assess basic standing function in non-ambulatory subjects, we will employ a standardised standing test on a force plate. The subject will be requested to: (1) stand in bipedal stance, (2) shift his/her body weight from the right to the left leg alternately, and (3) shift his/her body weight in a defined rhythm from the right to the left leg alternately. The test-retest reliability of centre of pressure measures in bipedal tasks has been shown previously [30]. We will use the Stroke Impact Scale (SIS) to assess recovery and quality-of-life after stroke [31].

**Table 1 T1:** Overview of primary and secondary outcomes

**Variable**	**Details**	**Unit**

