**Figure 3 F3:**
[figure not shown]
**Exercise testing protocols.** Schematic representation of constant load testing **(A)** and incremental exercise testing **(B)** using feedback-controlled robotics-assisted treadmill exercise. The solid line represents the mechanical work rate (*P*_*mech*_) produced by the subject. The dashed line represents the target work rate (*P**_*mech*_). The slope will be estimated such that the predefined peak work rate is reached after 10 minutes. When individual termination criteria are met the incremental phase is ended and *P**_*mech*_ set back to the passive level.

Incremental exercise testing (IET) [35] will be used to estimate peak cardiopulmonary performance parameters. Figure 3B shows a schematic representation of the IET protocol that consists of: (1) a passive phase where subjects will be instructed to walk passively with their individual BWS for 5 minutes; (2) and active phase where subjects will be instructed to actively contribute to the walking by pushing forward within the exoskeleton during the swing phase of each leg to reach peak exercise capacity, where the slope will be defined so that MVC-W is reached in approximately 10 minutes; and (3) a passive phase/recovery where subjects will be instructed to walk passively with their individual BWS for 5 minutes.

Both test protocols will follow strict termination criteria for cardiopulmonary exercise testing including: (1) abnormal blood pressure responses, that is, hypertensive (systolic BP >210 mmHg or diastolic BP >115 mmHg) when exercising at high work rate, or hypotensive responses (decrease in BP >10 mmHg) despite an increase in work rate; (2) individual work rate below target work rate for 60 s; (3) peak heart rate within 10 beats per minute of the age-predicted heart rate maximum [36], where the formula will be adjusted down to 70% of heart rate maximum for subjects on β-blocker medications [37]; and (4) pain or discomfort in the chest. We will follow established models for cardiopulmonary exercise testing based on the ACSM guidelines [24].

The 10MWT and the 6MWT will be conducted using standardised testing protocols in a quiet area. Standing function will be assessed within parallel bars. The SIS will be administered to the subjects on a face-to-face basis.

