### Statistical analysis

Descriptive statistics will be calculated for dependent and independent variables. Demographic and clinical characteristics of the groups will be compared on admission using unpaired two-sample *t*-tests (continuous data) and Chi-square analysis (categorical data). Nonparametric methods will be used when assumptions of normality are violated. To evaluate the clinical efficacy of the method, group differences will be compared after each 4-week intervention (t1, t2, t3, *etcetera*) using unpaired two-sample *t*-tests for continuous data and z-tests for categorical data that conform to the assumption of normality. If data are not normally distributed for continuous variables, Mann-Whitney *U* tests will be applied. A mixed effects analysis of variance with repeated measures to model the intervention effects over time for continuous variables that are normally distributed (that is, aerobic capacity) will be applied. Non-parametric tests (Mann-Whitney *U* and Kruskall Wallis tests) will be used for categorical data (that is, SIS) or where a normal distribution is not present. Variables that are significantly different in the baseline analysis will be used as covariates for further analysis. Multiple regressions will be applied to evaluate relationships among variables. All statistical analysis will be performed using SPSS (SPSS Inc., Chicago, Il, USA). The significance level will be 0.05.

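### The plan gives no gait-speed value to a subject who cannot walk 10 m, so in a non-ambulatory population the 10MWT comparison would lose subjects according to their outcome

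*Protocol article*

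**What the plan says.** Under Eligibility criteria: "Subjects will be enrolled after their first stroke if they are non-ambulatory". The operational criterion is "Functional Ambulation Category (FAC) ≤3"; the article does not define the levels of that scale.

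Under Outcome measures: "Gait speed will be assessed using the 10 Meter Walk Test (10MWT"), which Table 1 lists as a secondary outcome in m/s. Walking endurance is the 6MWT in metres, described as "the distance that an individual is able to walk in 6 minutes on a hard, flat surface". The timing covers everyone: "All primary and secondary outcome measurements will be carried out at baseline (t0), after each 4-week intervention period", and again before discharge. One outcome is adapted to the population: "To assess basic standing function in non-ambulatory subjects, we will employ a standardised standing test on a force plate".

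On conduct, the Testing procedure section says only: "The 10MWT and the 6MWT will be conducted using standardised testing protocols in a quiet area". Under Statistical analysis, "group differences will be compared after each 4-week intervention" by unpaired t-test, or by Mann-Whitney test if the data are not normal. A repeated-measures mixed-effects analysis of variance is added for normally distributed continuous variables.

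The article does not say what is recorded when a subject cannot do a walking test, or whether that subject enters the comparison.

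**The concern.** Speed over 10 m is distance divided by time. A subject who does not cover the distance has no time, hence no speed. With no assigned value, the entry is blank, and a t-test or Mann-Whitney test leaves out a blank. The repeated-measures model also has nothing for that subject at that visit.

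Who is blank is not random. Being able to walk at week 4 or 8 arises after randomisation, and it is the recovery that the outcome is meant to capture. If FC-RATE helps more people to walk, its extra walkers are probably its slowest, and they enter only its own mean. A subject who moves from not walking to walking slowly then lowers the experimental arm's average. In the controls, those who still cannot walk count for nothing.

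Motor recovery is part of the trial's first aim, and the results are to inform larger trials (third aim). A diluted estimate from a few walkers would mislead on both.

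**Working it through.** **Figures in the plan.** The article gives no SD, effect or walking share for the 10MWT, so there is no figure to reproduce. Its sample size (at least 14, recruiting 20) is not tied to gait speed and does not bear on this point. I take 10 per arm from 20 recruited, assuming equal allocation. All other inputs are assumptions.

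**Model.** Latent walking capacity is normal with mean μ and SD σ = 0.4 m/s. A subject walks if it exceeds 0, and speed then equals it. The experimental mean is 0.4 m/s above control. With φ and Φ the standard normal density and distribution function:

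- share walking: p = Φ(μ/σ)
- mean among walkers: m = μ + σ·φ(μ/σ)/p
- mean with inability scored 0: p·m

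**Setting A, 50% of controls unable to walk.**

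- Control, μ = 0: p = 0.500; m = 0.4 × 0.3989/0.500 = 0.319; p·m = 0.160.
- Experimental, μ = 0.4: p = 0.841; m = 0.4 + 0.4 × 0.2420/0.841 = 0.515; p·m = 0.433.
- Difference: walkers only 0.515 − 0.319 = 0.20 m/s; zero-scored 0.433 − 0.160 = 0.27 m/s.

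**Setting B, 69% of controls unable to walk.**

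- Control, μ = −0.2: p = 0.309; m = −0.2 + 0.4 × 0.3521/0.309 = 0.256; p·m = 0.079.
- Experimental, μ = 0.2: p = 0.691; m = 0.2 + 0.4 × 0.3521/0.691 = 0.404; p·m = 0.279.
- Difference: walkers only 0.404 − 0.256 = 0.15 m/s; zero-scored 0.279 − 0.079 = 0.20 m/s.

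**Power by simulation** (10 per arm, two-sided 0.05; a trial with fewer than two walkers in an arm counts as not significant). Repeat runs differ by a few points.

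| | Setting A | Setting B |
|---|---|---|
| Walkers-only t-test | 16% | 7% |
| Zero-scored Mann-Whitney | 48% | 45% |
| Zero-scored t-test | 49% | 43% |
| Trials with fewer than two walkers in an arm | about 1% | about 14% |

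**Other assumed walking shares** (same SD, 3,000 trials each):

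| Walking, control vs experimental | Walkers-only t-test | Zero-scored Mann-Whitney |
|---|---|---|
| 30% vs 30% (no effect) | 0.035 | 0.037 |
| 30% vs 60% | 0.05 | 0.28 |
| 50% vs 80% | 0.13 | 0.37 |
| 30% vs 80% | 0.11 | 0.72 |
| 20% vs 80% | 0.09 | 0.86 |

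With no effect, both reject at a similar rate, below 0.05. The loss appears when treatment changes who walks.

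**Constructed illustration.** Three of 10 controls walk, at 0.4, 0.5 and 0.6 m/s. The experimental arm has the same three plus three new walkers at 0.2 m/s.

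- Walkers only: control 1.5/3 = 0.50; experimental 2.1/6 = 0.35.
- All ten, zero-scored: control 1.5/10 = 0.15; experimental 2.1/10 = 0.21.

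Leaving out non-walkers makes the arm with twice as many walkers look worse.

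**The case against.** **The text excludes nobody.** This is the strongest objection, and it stands as a limit on wording. All outcomes are due for all subjects, and groups are compared, not walkers. A reader might infer that the plan rests its test on those who regain walking; the article does not say so. The loss follows only because a missing speed cannot enter the stated tests.

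**A scoring rule may sit in a full protocol, test manual or SAP that is not shown.** It may. But the article itself fixes the population, unit, visits and test, and for that population the unit can be undefined. It adapts the standing test to non-ambulatory subjects and does not do the same for the 10MWT.

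**The 6MWT is already defined for non-walkers.** Largely right: a distance one is able to walk can be 0 m. Only an explicit statement is lacking, so the point is mainly about the 10MWT.

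**FAC ≤3 does not mean nobody can walk 10 m.** Right. The levels are undefined in the article, some subjects may be testable at entry, and the affected share is unknown.

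**The effect shrinks; it does not reverse.** Right for the average in the model. In single simulated trials the walkers-only difference has the wrong sign in roughly 10% (A) and 17% (B), which reflects few walkers. Average reversal needs slow new walkers, as in the constructed case. The fair yardstick is also the zero-scored difference (0.27 or 0.20 m/s), not the latent 0.4 m/s.

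**The rank test adds little.** Right: a t-test on zero-scored values has similar power. The gain comes from the scoring.

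**Conclusion.** The concern holds in a limited form. The plan compares 10MWT speed between arms in a population enrolled as non-ambulatory and gives no value to a subject who cannot walk 10 m. Applied as written, the tests would lose such subjects on a basis that is post-randomisation and tied to the outcome. That would shrink a true recovery effect and cost power.

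On the assumed inputs, the difference falls by about a quarter (0.27 to 0.20 m/s in A, 0.20 to 0.15 in B), and power falls from just under one half to 16% or 7%. The size rests on the assumed SD, shift and walking shares; if nearly all subjects can cover 10 m, it is small.

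A reader might infer that the plan hides recovery or will give the wrong sign. The documents do not support that: it depends on how non-walkers are handled, which is not stated, and on how fast new walkers are. For the 6MWT only a stated zero is missing. As these are secondary outcomes of a 20-subject pilot that also has a standing test and the SIS, this should be corrected but does not threaten the primary outcome.

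**What to change.** Add to Outcome measures that a subject unable to complete the test is scored 0 m/s on the 10MWT, and that a subject unable to walk is scored 0 m on the 6MWT. Add to Statistical analysis that both comparisons include every randomised subject assessed at the visit and use the Mann-Whitney test already planned for non-normal data, corrected for ties. A block of zeros makes normality untenable, so this names in advance the test that the plan's own rule would reach. Report beside it the number able to walk in each arm; that figure is also useful for planning a larger trial. A subject who was not assessed at all stays missing and is not scored 0.

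The cost is a few sentences and no new data. The small downside is that the result is a rank comparison with ties at zero, not a mean speed difference among walkers; speeds of those who walk can still be described.
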